### Outcomes {12}

The primary outcome is the proportion of participants who have died (all-cause mortality) or received massive transfusion in the first 24 h from randomisation. A participant is considered randomised and entered into the trial when the trial intervention box has been opened.

For the purposes of analysis, two units of whole blood will be counted as equivalent to four total units due to the volume difference between the intervention and control arm, the fact that two units of whole blood contain the equivalent of two units of plasma plus two units of packed RBCs, and for the massive transfusion part of the primary analysis, both arms will start will an equal baseline.

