Secondary outcomes include the following: the proportion of participants who received massive transfusion (for adults, a total of 10 or more units of any blood components) in the first 24 h from randomisation; all-cause mortality at 6 h, 24 h, 30 days, and 90 days from randomisation; number of organ failure-free days up to 30 days, defined as the number of days free of advanced cardiovascular, advanced respiratory, and advanced renal support; days in critical care and separately in an acute care hospital (up to 90 days); units of each blood component received in the 24 h after randomisation, including pre-hospital transfusions (WB, RBC, plasma, platelets, and cryoprecipitate); amount of cell salvage received at 24 h (in ml) after randomisation; number of participants receiving additional haemostatic agents received at 24 h after randomisation (recombinant factor VIIa, fibrinogen concentrate, prothrombin complex concentrate (PCC), tranexamic acid (TXA)); presence of coagulopathy (defined as prothrombin time above the normal range) in the first sample taken on arrival at an acute care hospital; acid-base disturbance measured by lactate, base excess, and pH level in first sample taken on arrival at acute care hospital; cost of provision of the whole blood intervention; hospital resource use up to discharge or death, including ventilator days, days spent in critical care, and total in-patient stay; health, social, and wider care service resource use to 90 days after injury; health-related quality of life (EuroQol 5 Dimension 5 Level, EQ-5D-5L) at 90 days after injury; thrombosis (arterial and venous) up to 30 days after randomisation or hospital discharge or death, whichever is first; and all transfusion reactions/events relating to pre-hospital blood components which have been reported to SHOT (Serious Hazards of Transfusion) in the first 14 days after randomisation.

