## Statistical methods

### Statistical methods for primary and secondary outcomes {20a}

Analyses will be described in detail in a full statistical analysis plan (SAP). This section summarises the main points.

The following factors will be used to assess baseline comparability of the randomised groups:
◦ Age in years, reported as a median (IQR)◦ Number and proportion of paediatric participants (defined as < 16 years)◦ Sex (male or female)◦ Type of injury (blunt or penetrating)◦ Nature of traumatic injury (high or low energy transfer)◦ Injury Severity Score, reported as a median (IQR), defined as the sum of the squares of the highest AIS grade in each of the three most severely injured areas. Note if the participant is dead upon arrival to hospital, then the ISS is not calculated and hence will be assumed to be 75 (the maximum score) [24].◦ Systolic blood pressure (mm Hg), reported as a median (IQR)◦ Heart rate (per minute), reported as a median (IQR)◦ Glasgow Coma Scale, reported as a median (IQR). This score measures eye opening, verbal and motor response functions◦ Age of blood in days, reported as a median (IQR). This will be determined using routinely collected NHSBT data.

A CONSORT diagram will be produced to show the flow of participants through the trial.

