#### Primary outcome

The primary outcome will be determined as the proportion of participants who have either died (from all causes) or received 10 or more units of blood components, within the 24 h from randomisation (a participant is considered randomised and entered into the trial when the trial intervention box has been opened). The following will be included in the blood component count: RBC, platelets, whole blood, thawed plasma (or LyoPlas), and cryoprecipitate. In this trial, for the purposes of analysis, two units of whole blood will be counted as equivalent to four total units due to the volume difference between the intervention and control arm, the fact that two units of whole blood contain the equivalent of two units of plasma plus two units of packed RBCs, and for the massive transfusion part of the primary analysis, both arms will start will an equal baseline. The composite outcome will be analysed using a mixed logistic regression model with adjustment for AAS, fitted as a random effect. A superiority hypothesis will be tested and the results from the adjusted analysis will be considered the primary analysis.

All analyses will be performed on a modified intention to treat basis, to exclude participants who experience a traumatic cardiac arrest, but will include all other randomised patients on whom a value of the response variable has been obtained, including those randomised in error and regardless of the participants’ adherence to the protocol. The data will be presented and analysed according to the arm to which the participant was randomised, regardless of whether they received the randomised intervention or not.

The primary outcome will be replicated per protocol, which will exclude participants who experience a traumatic cardiac arrest, those who experience a protocol deviation, were randomised in error or were withdrawn from the trial. The data will be presented and analysed according to the arm to which the participant was randomised.

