#### Secondary outcome analysis

All-cause mortality at 6 h, 24 h, 30 days, and 90 days, the proportion of participants who receive 10 or more units of any blood components, and presence of coagulopathy will each be analysed separately using the same model that is described for the primary outcome.

Organ failure-free days and days in critical care and an acute care hospital will be reported as a median and IQR, by treatment arm and overall.

Units of each blood component received in the 24 h after randomisation will be summarised with a median and interquartile range and analysed using a negative binomial model, with adjustment for AAS.

Amount of millilitres (ml) of cell salvage at 24 h after randomisation and lactate, base excess, and pH level in first sample taken on arrival at acute care hospital will be analysed separately using a mixed linear regression model, with adjustment for AAS.

For each of the additional haemostatic agents, the number of participants who received each agent will be presented by trial arm and overall.

Thrombosis (arterial or venous thrombosis) up to 30 days after randomisation (or death or hospital discharge, whichever is first) and transfusion reactions/events relating to pre-hospital blood components which have been reported to SHOT (Serious Hazards of Transfusion) occurring in the first 14 days after randomisation will be summarised.

The economic evaluation will establish the resources required to provide the whole blood intervention, estimate intervention as compared to standard care costs, and conduct a full incremental cost-effectiveness analysis. Analyses will be undertaken against a primary perspective of the NHS/Social Care. Cost and outcome data will be synthesised to present incremental cost-effectiveness ratios for the primary outcome and cost per quality-adjusted life-year at 90 days. Multivariable regression analyses and bootstrapping will be employed, uncertainty will be explored, and cost-effectiveness acceptability curves will be presented. The internationally recognised CHEERs guidelines will be followed, and planned analyses will be described in a health economics analysis plan, which will be fully concordant with the SAP.

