### Methods in analysis to handle protocol non-adherence and any statistical methods to handle missing data {20c}

Protocol deviations will be monitored throughout the trial and will be assessed as minor or major and whether they influence the statistical analysis. For the primary analysis, any missing data for the primary and secondary outcome measures will be treated as missing data and not be imputed. If an outcome has data missing for more than 25% of participants, then the analysis will not be undertaken. All missing primary and secondary outcome data will be summarised.

A sensitivity analysis will be conducted if the primary outcome is missing for more than 5% of participants, which will impute the composite endpoint.

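### Coagulopathy, lactate, base excess and pH are compared only in participants who survive to hospital and are sampled, so unequal early death would bias them against the better-surviving arm

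*Protocol article*

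**What the plan says.** All references are to the protocol article.

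- **Time zero.** Outcomes {12}: "A participant is considered randomised and entered into the trial when the trial intervention box has been opened". This happens at the scene.
- **Measurement.** The same section defines one secondary outcome as "presence of coagulopathy (defined as prothrombin time above the normal range) in the first sample taken on arrival at an acute care hospital" and another as "acid-base disturbance measured by lactate, base excess, and pH level in first sample taken on arrival at acute care hospital".
- **Models.** Secondary outcome analysis states that mortality, massive transfusion and "presence of coagulopathy will each be analysed separately using the same model that is described for the primary outcome", which is a mixed logistic regression with air ambulance service as a random effect. Lactate, base excess and pH get mixed linear models adjusted for air ambulance service.
- **Analysis set.** Primary outcome: "All analyses will be performed on a modified intention to treat basis, to exclude participants who experience a traumatic cardiac arrest". The set otherwise "will include all other randomised patients on whom a value of the response variable has been obtained".
- **Missing values.** Section {20c} says, for the primary analysis, that "any missing data for the primary and secondary outcome measures will be treated as missing data and not be imputed". An outcome with more than 25% missing is not analysed. The only imputation analysis described is for the composite endpoint.
- **Death before arrival is foreseen.** In the baseline list of section {20a}: "Note if the participant is dead upon arrival to hospital, then the ISS is not calculated", and the maximum score of 75 is then assumed. No corresponding rule is given for the four arrival measurements.

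**The concern.** Arrival at hospital alive, and being sampled there, are events after randomisation that treatment may influence. Those who die first are likely to include some of the most coagulopathic and acidotic participants. If one arm keeps more of them alive until sampling, it contributes extra badly deranged samples, while their counterparts in the other arm disappear from the analysis.

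The possibility is not remote. The sample size section motivates the trial partly with studies reporting lower 24-h mortality (4% vs 12% with whole blood; an 11% absolute difference with platelets). Section {20b} has a category for transport times over 20 minutes. The four measurements are the trial's early laboratory evidence on haemostasis and perfusion, so bias here could distort the account of how whole blood works.

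**Working it through.** The documents state no figure on this point, so there is none to reproduce. Every rate below is an assumption, apart from 301 per arm, which is half of the stated 602.

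**Step 1: a closed-form upper-end case.** Let dc and dw be the proportions dying before the sample on control and whole blood, and p the coagulopathy prevalence among those who would be sampled under either arm. Treatment has no effect on coagulopathy in that group. Let q be the prevalence among the extra whole-blood survivors.

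Observed on control: p. Observed on whole blood: [(1 − dc)p + (dc − dw)q] / (1 − dw).

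Spurious difference: (dc − dw)(q − p) / (1 − dw).

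Take p = 0.30 and, at the extreme, q = 1. For lactate, use a mean of 6 mmol/L in the others and 15 in the extra survivors.

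| dc vs dw | Coagulopathy excess | Lactate difference |
|---|---|---|
| 5% vs 3% | 0.02 × 0.70 / 0.97 = 1.4 points | 0.02 × 9 / 0.97 = +0.19 mmol/L |
| 10% vs 6% | 0.04 × 0.70 / 0.94 = 3.0 points | 0.04 × 9 / 0.94 = +0.38 mmol/L |
| 15% vs 10% | 0.05 × 0.70 / 0.90 = 3.9 points | 0.05 × 9 / 0.90 = +0.50 mmol/L |

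The formula also shows the conditions. The bias is zero if dc = dw or if q = p, and it runs against whole blood only if dw < dc and q > p.

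**Step 2: graded severity.** A simulation of one million draws per scenario replaces the extreme assumption.

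- Latent severity is standard normal, and the log odds of death before sampling rise by 1.5 per unit.
- The biomarker correlates with severity at 0.3, 0.6 or 0.9.
- Coagulopathy is the top 30% of the biomarker in the whole population.
- Treatment has no effect on the biomarker.

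| Death before sample, control vs whole blood | Standardised difference (worse on whole blood) | Coagulopathy odds ratio |
|---|---|---|
| 3% vs 3% | 0 / 0 / 0 | 1.00 / 1.00 / 1.00 |
| 3% vs 1% | 0.008 / 0.016 / 0.024 | 1.01 / 1.03 / 1.05 |
| 5% vs 2% | 0.011 / 0.022 / 0.033 | 1.02 / 1.04 / 1.07 |
| 10% vs 5% | 0.017 / 0.034 / 0.051 | 1.03 / 1.07 / 1.12 |
| 10% vs 2% | 0.028 / 0.057 / 0.085 | 1.05 / 1.12 / 1.19 |
| 15% vs 7% | 0.026 / 0.052 / 0.078 | 1.05 / 1.11 / 1.19 |

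With 301 randomised per arm, a nominal 5% two-sided test of the continuous biomarker rejects falsely in 6%, 10% and 17% of trials at 10% vs 2%. At 5% vs 2% the figures are 5%, 6% and 7%.

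**Step 3: what counting death does.** Take 10% vs 6% with p = 0.30 and score death before sampling as an event.

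- q = 1: control 0.10 + 0.90 × 0.30 = 0.37; whole blood 0.06 + 0.90 × 0.30 + 0.04 × 1 = 0.37. The spurious excess is gone, but a 4-point survival gain is hidden.
- q = 0.5: control 0.37; whole blood 0.06 + 0.27 + 0.02 = 0.35. The sampled-only comparison would show (0.27 + 0.02) / 0.94 = 30.9% vs 30.0%, which points the other way.

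**Step 4: the cardiac-arrest exclusion.** The Primary outcome section does not say when the arrest must occur. If only arrests at or before box opening count, participants who die later and before sampling stay in the set without a value. If later arrests count, the exclusion is itself selection after randomisation. Neither reading restores the randomised comparison.

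**The case against.** The strongest reply is that the exclusion of traumatic cardiac arrest, expected to affect 25% of participants, probably removes many of those who die at the scene or in transit. The injury-score rule shows that death before arrival is foreseen, but not how many such deaths remain in the analysed set. This stands as a limit on size: nothing in the documents supports any particular rate. It does not remove the mechanism (Step 4).

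It can also be said that the article only summarises the methods, that the no-imputation rule is confined to the primary analysis, and that missing outcome data will be summarised. That leaves room for more in the analysis plan. Yet the article itself fixes the population, the models and the handling of absent values for these outcomes, and together they give the conditional comparison. The summary of missing data helps, but the article does not say that it will be by arm and by reason. The 25% cut-off does not protect, because the bias arises well below it.

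Mortality at 6 h and 24 h is analysed separately, so a reader could see unequal early death beside the biomarkers. That aids interpretation but does not correct the estimates.

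Two stronger readings are tempting. A reader might infer that whole blood's biomarkers will look worse. The documents do not support that: it needs fewer deaths before sampling on whole blood, sicker extra survivors, and no true benefit large enough to outweigh the bias. A reader might also take the 3 to 4 points or 0.5 mmol/L of Step 1 as the likely size. Those figures rest on every extra survivor being coagulopathic, with lactate of 15.

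**Conclusion.** The concern holds as a conditional one. As written, the four comparisons are restricted to participants who survive to hospital and are sampled. If death before sampling differs by arm, they are not comparisons of randomised groups, and they are biased against the arm with better early survival when those saved are sicker than average.

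The size cannot be fixed from the documents. Over the graded assumptions with unequal early death, it is a standardised difference of about 0.01 to 0.09 and a coagulopathy odds ratio of about 1.01 to 1.19; with equal early death it is nil. These are secondary outcomes, and the primary composite is unaffected. The change is worth making because it is cheap, but the trial's main conclusion does not depend on it.

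**What to change.** For these four outcomes:

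1. Add an analysis of prolonged prothrombin time or death before the first sample, with the same mixed logistic model.
2. For lactate, base excess and pH, add a ranked analysis that puts death before sampling at the worst rank.
3. Run both in a set whose cardiac-arrest exclusion is limited to arrests at or before box opening, or which otherwise includes deaths after box opening. Without this, the added analyses cannot count deaths that the current exclusion may remove.
4. Keep the sampled-only models, labelled as conditional on arrival and sampling.
5. Report by arm the number unsampled because of death and the number unsampled for other reasons, and treat only the latter as missing.

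The cost is wording and a little extra analysis. The composite is a less pure biomarker and can mask a survival gain (Step 3), so it should be shown beside the sampled-only result and mortality.

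One point needs confirming. Section {18a} lists alive/dead status at 6 h and 24 h, but not time of death, sample time or reason for no sample. The injury-score rule implies that death on arrival is known; death after arrival but before sampling may not be. The sponsor should check that death before the sample can be identified from the data collected.

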### Criteria for discontinuing or modifying allocated interventions {11b}

If the trial intervention has not been completed by the time the participant arrives in hospital, it should be completed after arrival at hospital if it is still clinically indicated. Further management is dictated by normal clinical protocols. If bleeding continues and further fluid resuscitation is needed, additional blood components will be administered as per standard care and as required, following the initial trial components. All blood components will be given according to local standard policies on the use of blood warmers.

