## Assignment of interventions: blinding

### Who will be blinded {17a}

The AAS clinical teams will be blinded to the randomised allocation until the trial box is opened, after which point it is not feasible to maintain blinding. To ensure that the team can remain blinded until the box is opened, the boxes containing intervention or control will be the same size and shape. It is not possible to blind the team at the receiving hospital to the intervention.

Participants will be blinded to allocation until the trial box is opened, but they may discover this information post-randomisation (e.g. by reading their medical notes or requesting this information from the Research Team), although there is no obligation to inform the participant which treatment they received.

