## Data collection and management

### Plans for assessment and collection of outcomes {18a}

On arrival at hospital, the AAS clinical team will hand over clinical responsibility for the participant to the receiving hospital team and complete the pre-hospital form (on the eCRF). Each unit of blood administered pre-hospital will be recorded on the eCRF, along with the donation number (G number) of the unit and the transfusion start time.

The principal investigator and research team at the receiving hospital will be responsible for collecting the clinical data for trial participants.

The transfusion laboratory at the receiving hospital will be responsible for recording the final ‘fate’ of all blood components that were administered to the participant, to ensure full traceability.

Data to be collected by the research team at 24 h post-randomisation include the following: participant demographics and baseline data, participant status (alive/dead) at 6 h and 24 h, total number of blood components transfused, cell salvage/autologous blood transfusion, and any haemostatic agents received.

Data to be collected by the research team at 30 days post-randomisation include participant status (alive/dead), total number of blood components transfused, critical care unit admission (yes/no), plus date/time of admission where applicable, hospital resource use (up to discharge from acute care hospital or death, whichever is first), thromboembolic events (clinically diagnosed), and any transfusion reactions which have been reported to SHOT (occurring in first 14 days post-randomisation).

For participants that are alive at 90 days post-randomisation, data collected will include participant status (alive/dead), health-related quality of life questionnaire (EQ-5D-5L, or EuroQol 5 Dimension Youth, EQ-5D-Y for participants aged 5–14 years), and health, social, and wider care service use questionnaire. Limited patient identifiable information will be collected to enable linkage to the Trauma Audit and Research Network (TARN) and Intensive Care National Audit and Research Centre (ICNARC) routinely collected data. This will prevent duplicate data collection and reduce the burden of data collection for hospital research teams.

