### Adverse event reporting and harms {22}

SWiFT trial participants have suffered traumatic injury and by definition will have multiple (serious) adverse events during their transfer to hospital and admission (related to their traumatic injury). Most of the AEs occurring in SWiFT, whether serious or not, will therefore be anticipated in the sense that they are recognised and accepted complications/consequences of major trauma.

All serious adverse events/reactions which relate to the administration of the pre-hospital WB, standard of care components (RBC and FFP), or LyoPlas will be reported as serious adverse events.

Any unused units will be disposed of in accordance with local requirements. For used products, all hospital transfusion laboratories are required by BSQR to keep the evidence of traceability for every unit used (or wasted) for 30 years. The following data items will be electronically recorded: donation number, component type, blood establishment which provided the blood component, date provided, identity of patient who received the blood component, or final fate if not transfused. Furthermore, transfusion laboratories have SOPs in place that accurately report any serious adverse events or reactions relating to blood transfusion to national haemovigilance systems (SHOT).

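### The transfusion-reaction outcome dates its 14-day limit by report in one section and by occurrence in two others, and its restriction to reactions linked to the pre-hospital units leaves differential attribution uncheckable from the planned summary

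*Protocol article*

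**What the plan says.** Three sections of the protocol article describe this outcome.

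- **Outcomes {12}** lists all "transfusion reactions/events relating to pre-hospital blood components which have been reported to SHOT (Serious Hazards of Transfusion) in the first 14 days after randomisation".
- **Plans for assessment and collection of outcomes {18a}** has the research team record "any transfusion reactions which have been reported to SHOT (occurring in first 14 days post-randomisation"). The item belongs to the day-30 form: "Data to be collected by the research team at 30 days post-randomisation include participant status (alive/dead"), with this item later in the same list. It carries no restriction to pre-hospital components.
- **Secondary outcome analysis** restores the restriction, "transfusion reactions/events relating to pre-hospital blood components which have been reported to SHOT", and then dates the event by onset: "occurring in the first 14 days after randomisation will be summarised". No model or test is named.

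Three other statements bear on how relatedness is judged.

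- Who will be blinded {17a}: "It is not possible to blind the team at the receiving hospital to the intervention".
- Criteria for discontinuing or modifying allocated interventions {11b}: if bleeding continues, "additional blood components will be administered as per standard care and as required, following the initial trial components".
- Adverse event reporting and harms {22}: "transfusion laboratories have SOPs in place that accurately report any serious adverse events or reactions relating to blood transfusion to national haemovigilance systems (SHOT"). The serious adverse event rule in the same section is also limited to events related to the pre-hospital products.

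**The concern.** There are two separate problems.

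**The date rule.** The outcome definition ties the 14 days to the report, while the other two sections tie them to the reaction. Two analysts working from different sections could count different events.

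**The relatedness condition.** A participant may receive hospital components soon after the trial units. Whether a later reaction relates to the pre-hospital units is then a matter of judgement. The hospital knows the arm, and the article describes no assessment of relatedness blind to arm. One arm receives a product that is not in routine NHS use. The other receives the kinds of component that hospitals give anyway. If the same reaction were attributed to the trial units more readily in one arm, equal true rates would appear unequal, or a true difference would be hidden. A table of attributed events alone cannot reveal this.

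Safety is a stated objective, and the trial is meant to inform wider use of whole blood. Rare product harms are usually read from descriptive tables of this kind, so the definition of the event matters even without a test.

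**Working it through.** The document gives no rate, margin or power for this outcome, so there is no figure of the plan to reproduce. The check is a comparison of the sections, followed by arithmetic on assumed values.

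**Step 1. Apply each section's wording to four hypothetical reactions.**

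| Reaction | Outcomes {12}, literal | Data collection {18a} | Secondary outcome analysis |
|---|---|---|---|
| Onset day 5, reported day 10, linked to pre-hospital unit | in | collected | in |
| Onset day 12, reported day 20, linked to pre-hospital unit | out | collected | in |
| Onset day 12, reported day 35, linked to pre-hospital unit | out | not yet known at day 30 | in as worded |
| Onset day 1, reported day 3, linked to hospital unit only | out | collected | out |

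The second row shows the date conflict. The third shows that the article sets no cut-off for accepting reports. The fourth shows that data for a count free of attribution are already planned but are not in the planned summary.

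**Step 2. What the attributed count measures.** Let r be the true rate of SHOT-reported reactions and a the proportion attributed to the pre-hospital units. The observed rate in an arm is r × a. If r is equal in both arms, then

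observed ratio (whole blood : control) = a(whole blood) / a(control).

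The document gives neither r nor a. Taking r = 4% and letting each a be 30% or 60%, all by assumption:

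- 60% against 30%: 0.04 × 0.60 = 2.4% and 0.04 × 0.30 = 1.2%, ratio 2.0
- equal attribution: ratio 1.0
- 30% against 60%: 1.2% and 2.4%, ratio 0.5

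The ratio only returns the assumed attribution. This shows that bias is possible in either direction. It is not an estimate.

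**Step 3. How sparse the events may be.** The planned analysable number is 602 (Sample size {14}), so 602 / 2 = 301 per arm. At assumed true rates:

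- 1%: 301 × 0.01 = 3.0 events per arm
- 2%: 301 × 0.02 = 6.0
- 5%: 301 × 0.05 = 15.1

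With 3 to 15 events per arm, moving two or three by the date rule or by attribution would visibly change the comparison.

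**The case against.** A fair defence has five parts.

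1. **The date difference is editorial.** In Outcomes {12} the closing time phrase could be read as qualifying the reactions and not the reports. Both operative sections date by occurrence, and collection at day 30 fits that. This largely stands. A reader might infer that late reports are lost by design, but they are lost only under the literal wording of the definition. The wording should still be corrected, because the definition is where a reader looks first.

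2. **Collecting any reaction and analysing a related subset is ordinary practice.** This stands, and it makes the remedy cheap. It does not make the subset checkable unless the full count is also shown.

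3. **The document does not say who assesses relatedness.** A reader might infer that unblinded receiving clinicians decide which unit caused a reaction. The document does not say so: it says that this team cannot be blinded, and it names transfusion laboratories as the SHOT reporters. Nor does it support a claim that whole blood is more likely to be blamed. The supportable statement is narrower: no blinded assessment is described, so differential attribution is possible.

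4. **Stronger numbers do not hold.** In a control participant with exactly 10 units, at most 4 came from the trial box. One might infer that attribution is right at most 40% of the time. But at equal risk per unit, always naming the hospital units would be right 6 / 10 = 60% of the time. Donation number and start time are also recorded for each pre-hospital unit. Likewise, the 68% planning rate combines death with 10 or more units and is not split, so it does not give the proportion who receive many hospital units.

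5. **An all-reactions count is not a cleaner version of the same outcome.** Sample size {14} and the Discussion expect whole blood to reduce later transfusion. If it does, exposure to hospital units differs by arm and the all-reactions count reflects that too. Unblinded recognition and reporting to SHOT would also remain. This stands, and it is why the wider count should accompany the attributed one and not replace it.

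**Conclusion.** The point holds in a limited form. The conflict between reporting date and occurrence date is on the page and needs correcting. The relatedness condition makes differential attribution possible, and the planned summary would not allow a reader to look for it. Size and direction cannot be derived from the document: the 30% and 60% attribution values and the 1% to 5% rates are assumptions. The number of events affected by the date wording depends on a reporting lag that is not given.

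The reach is modest. The analysis is a descriptive summary, thrombosis and all-cause mortality carry no relatedness condition, and the primary result is untouched. It would be wrong to infer that the safety comparison is biased. The supported conclusion is that the outcome is defined inconsistently and that a possible bias would go unseen.

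**What to change.** 1. In Outcomes {12}, tie the 14 days to the date of the reaction, as the data collection and analysis sections already do. State that reports are accepted up to the day-30 data collection, or name a later cut-off.
2. In Secondary outcome analysis, summarise by randomised arm all SHOT-reported reactions that occur within 14 days of randomisation, whichever component is suspected. Keep the pre-hospital-related outcome beside it.
3. Add a note that the two lines are to be read together, because the wider count also reflects any difference between arms in later hospital transfusion.

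The cost is wording in two sections and one extra table row. No new data are needed, since {18a} already collects any SHOT-reported reaction. Assessment of relatedness blind to arm would help further where practicable, but the correction does not depend on it.
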